#### Care as usual

The OPs in the control group do not receive additional training. They provide care as usual to workers on sick leave. In the Netherlands this means that the OP guides the sick-listed worker during sickness absence, recovery, and RTW. In this process the OP makes a diagnosis, assesses the ability to work, gives advice on work adaptations to the worker and the work environment, and provides relapse prevention. Although OPs are expected to work in accordance with the Dutch guideline, their actual adherence is low [12,13].

The extent of guideline adherence of the participating OPs will be measured by auditing the medical records of workers.

### Recruitment of OPs

All 66 participating OPs were recruited between October 2010 and January 2011 from the collaborative OHS. A researcher presented the study during OP meetings at several agencies of the OHS, provided written information about the study, and provided a registration form and informed consent. OPs participated on a voluntary basis; after completing the training the OPs in the intervention group received educational credits.

### Recruitment of participants

The study is conducted in the southern part of the Netherlands. The workers eligible for this study are on sick leave due to CMD diagnosed by the OP, counselled by an OP participating in the study, have had a first meeting with the OP, and are aged 18–65 years. From all eligible workers data on sick leave and RTW will be extracted from the registration system of the OHS anonymously.

Workers eligible for the data collection by means of the questionnaires work at one of the ± 320 companies served by this collaborating OHS that gave permission to invite their workers. The companies vary in size and serve different sectors. These workers are selected from the registration system of the OHS after their first consultation with the OP. They are sent an invitation letter from the OHS, as well as written information about the study. Workers who do not want to be contacted further can indicate this on a reply card. All eligible participants are contacted for additional information, and to check the inclusion and exclusion criteria. If the worker is willing to participate in the study and meets all the selection criteria, an informed consent and the baseline questionnaire will be sent to the worker.

Inclusion criteria for this study are: 1) CMD is the primary reason for sick leave diagnosed by an OP according to the Dutch Classification of Diseases (CAS) which is based on the ICD-10, 2) on current sick leave when selected from the registration system of the OHS after the first meeting with the OP, and 3) adequate command of the Dutch language. Exclusion criteria are: being suicidal, and a physical problem being the primary reason for sick leave at the time of study inclusion.

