### Study design

The study is designed as a two-armed cluster RCT with randomisation at the OP level (Figure 1). All participating OPs are recruited from a large collaborating OHS in the Netherlands. The OPs are randomised to an intervention group or a control group. Using an innovative training, OPs in the intervention group are trained to counsel sick-listed workers according to the Dutch national guideline ‘Management of mental health problems of workers by occupational physicians’. OPs in the control group receive no training and counsel sick-listed workers with care as usual. Workers are invited by the OHS after their first meeting with the OP. Data on sick leave and RTW of all invited workers are anonymously extracted from the registration system of the OHS during 1-year follow-up. In addition, in case of consent the worker receives a questionnaire at baseline (T0), and at 3 months (T1), 6 months (T2) and 12 months (T3) post baseline. In addition, 2 months after baseline a short questionnaire is sent to their supervisor.

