### Intervention

#### Intervention/guideline-based care

The Dutch guideline ‘The management of mental health problems of workers by occupational physicians’ promotes an activating approach of the OP as case and care manager to enhance the problem-solving capacity of the workers to achieve RTW. The guideline is based on cognitive behavioural principles to enhance the problem-solving capacity of workers in relation to their work environment, and process-based evaluation.

The guideline consists of four consecutive steps:

1) Problem orientation and Diagnosis: an early involvement of the OP is promoted (first assessment and start of counselling about 2 weeks after the worker reported sick). A simplified classification of mental health problems is introduced in four categories: i) Stress-related complaints, ii) depression, iii) anxiety disorder, and iv) other psychiatric disorders. Furthermore, problem inventory should focus on factors related to the worker and their work environment and the interaction between these two.

2) Intervention/Treatment: the OP acts as case manager by monitoring and evaluating the process of recovery (process-based evaluation). When recovery stagnates OPs should intervene by acting as care manager by using cognitive behavioural techniques to enhance the problem-solving capacity of the worker, providing the worker and work environment with information/advice on the recovery and the RTW process, contact the general practitioner when problems remain the same or increase, and refer the worker to a specialised intervention when necessary. In addition, the OP should advise the work environment (e.g. supervisors, managers, human resource managers) how to support the worker and enhance the recovery and RTW process.

3) Relapse prevention: Integration of relapse prevention from the first contact with the worker by enhancing the problem-solving capacity of the worker.

4) Evaluation: During follow-up meetings evaluation of the recovery process includes the perspectives of the worker, supervisor, and other involved professionals. Follow-up meetings with the worker should take place every 3 weeks during the first 3 months, and then every 6 weeks thereafter. The supervisor or work environment should be contacted once a month. Follow-up contacts with the general practitioner or other professionals should take place when the recovery process stagnates or when there is doubt about the diagnosis or treatment.

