#### Prognostic measures

•Personal characteristics such as age, gender, level of education, sick leave in the previous year, history of mental disorders, and expectations about full RTW are measured at baseline.

•Work characteristics such as number of working hours, contract type, type of work, profession and job content are measured at baseline. Job content is measured with the Dutch version of the Job Content Questionnaire (JCQ) [25], a self-report questionnaire which measures the social and psychological characteristics of jobs. The JCQ assesses the following scales: psychological job demands, decision latitude, social support, physical demands and job insecurity.

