### Randomisation

Randomisation takes place at the OP level, because workers cannot be randomly allocated to an OP in the intervention group or an OP in the control group since every OP is allied to a specific company. All participating OPs are randomised by computerised allocation to the intervention group or control group at OHS agency level.

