### Statistical analysis

Survival analyses will be used to analyse the primary outcome (time to full RTW) and the time to partial RTW comparing the intervention and the control group, while taking into account the effect of clustering of workers within OPs. Longitudinal multilevel analysis will be used to analyse the secondary outcomes.

To detect significant differences in the baseline characteristics between the intervention group and control group descriptive analyses will be used. If necessary these differences will be taken into account in the effect evaluation.

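### T0 follows the first consultation with the randomised OP, so adjusting for any significant T0 difference can remove part of the intervention effect

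*Protocol article*

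**What the plan says.** Allocation is at physician level: "Randomisation takes place at the OP level" (Protocol article, Randomisation). Workers enter afterwards. Under Study design, "Workers are invited by the OHS after their first meeting with the OP"; under Recruitment of participants, "These workers are selected from the registration system of the OHS after their first consultation with the OP". An invitation letter, a contact and an eligibility check follow. Only then, for workers who agree, does the protocol say that "an informed consent and the baseline questionnaire will be sent to the worker".

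The guideline places content in that first contact. Step 1 describes "first assessment and start of counselling about 2 weeks after the worker reported sick", and step 3 describes "Integration of relapse prevention from the first contact with the worker by enhancing the problem-solving capacity of the worker" (Intervention/guideline-based care).

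Table 1 lists diagnosis by the OP, RTW expectations, job content, symptoms, burnout and workability at T0. The Prognostic measures section repeats that "history of mental disorders, and expectations about full RTW are measured at baseline".

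The Statistical analysis section looks for significant differences in baseline characteristics between the arms and adds: "If necessary these differences will be taken into account in the effect evaluation". It does not restrict this to variables that precede the first consultation.

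**The concern.** A baseline covariate is safe to adjust for when the intervention cannot have changed it. Here T0 comes after the worker has met the randomised physician, so some T0 items may already carry an early effect of the training. A difference of that kind is not chance imbalance. Adjusting for it blocks the part of the effect that runs through the shifted variable.

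The significance trigger makes this worse. The items most likely to differ significantly at T0, and so to be adjusted for, include any that the training has moved. If the shift is favourable and the item predicts RTW, the estimate is pulled towards no effect. For the questionnaire outcomes, the same happens to whatever extent the longitudinal model conditions on T0.

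**Working it through.** **Step 1: order of events.** OP randomised; worker reports sick; first consultation; selection from the register; invitation; contact and eligibility check; consent form and T0 questionnaire. The gap between consultation and T0 is not stated. Table 1 also collects experience and satisfaction with the OP at T0, which presupposes that contact.

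**Step 2: which T0 items are exposed.**

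| T0 item | Could the first consultation change it? |
|---|---|
| Age, gender, education, previous-year sick leave, history of mental disorders, contract type, hours | No; these facts precede it |
| Diagnosis by the OP | Yes; the randomised physician makes it |
| RTW expectations, symptoms (4DSQ), burnout (UBOS), workability | Plausibly |
| Job content (JCQ) | Hard to see how |

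The primary outcome is taken from the register and counted from the first day of absence. It is exposed only through covariate adjustment, not through its definition.

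**Step 3: size for the primary outcome.** The protocol states no hazard ratio. Assuming proportional hazards, its return rates (Sample size) imply:

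- 6 months, 75% against 90%: ln(0.10)/ln(0.25) = 1.66, log HR 0.507.
- 3 months, 55% against 75%: ln(0.25)/ln(0.45) = 1.74, log HR 0.552.

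The T0 shift and the covariate's prognostic strength are assumptions. The simple product, shift × ln(HR per SD), gives:

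- 0.2 × ln(1.5) = 0.081; 0.081/0.507 = 16% (15% of 0.552).
- 0.3 × ln(1.6) = 0.141; 0.141/0.507 = 28% (26% of 0.552).

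These are shares of the log HR conditional on the covariate. They do not say how far the reported estimate moves between the unadjusted and the adjusted model. The hazard ratio is non-collapsible, so adjusting for a prognostic covariate also moves it away from zero. Simulated Cox models with a total conditional log HR of 0.507 and about 90% of control workers having the event give:

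| Assumed T0 shift | Covariate HR per SD | Adjusted against unadjusted log HR |
|---|---|---|
| 0 | 1.5 | about 12% larger |
| 0.1 SD | 1.5 | no loss |
| 0.2 SD | 1.5 | about 5 to 7% smaller |
| 0.3 SD | 1.6 | about 16 to 17% smaller |

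**Step 4: size for questionnaire outcomes.** Let f be the fraction of the final effect already present at T0 and r the correlation of T0 with the outcome, with equal variances. Change from T0 keeps 1 − f of the effect; covariate adjustment for T0 keeps 1 − r·f. Both f and r are assumed.

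| f | Change from T0 | Adjusted for T0, r = 0.5 | Adjusted for T0, r = 0.7 |
|---|---|---|---|
| 0 | 100% | 100% | 100% |
| 0.1 | 90% | 95% | 93% |
| 0.2 | 80% | 90% | 86% |
| 0.3 | 70% | 85% | 79% |
| 0.5 | 50% | 75% | 65% |

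Simulation at f = 0.3, r = 0.5 gave 71% and 86%, in line with the formulas.

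**Step 5: sample size.** It is unaffected. A two-sided pooled calculation gives 89 and 100 per arm. With 3.5 to 4 workers per OP and ICC 0.025 (design effect 1.0625 to 1.075) these become 95–96 and 107–108, close to the stated 97 and 110. Then 220/0.95 gives 232.

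**The case against.** The strongest reply is that harm needs two things the protocol does not establish: a shift produced by one consultation, and a model that conditions on the shifted item. The adjustment is only to be made if necessary, and no covariate is named. The contrast at visit one may be small. The guideline reserves cognitive behavioural techniques for stagnating recovery, and usual-care OPs also diagnose, assess work ability and provide relapse prevention. How far training has progressed matters too: the Abstract has it running during one year, while Content of the training has it received before the study starts. Those two statements need reconciling. All of this stands as a limit on size. It does not remove the fault in the rule, which draws no line between items before and after exposure.

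Second, workers enter after allocation and must still be on sick leave when selected. A T0 difference may therefore reflect differential selection or consent, in which case adjustment would protect. This also stands. The data cannot separate the two explanations, so T0-adjusted results should be kept, but not as the main analysis.

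Third, register data cover all eligible workers, whereas T0 questionnaire answers exist only for those who consent. Adjusting for expectations is not possible in the wider set. That narrows the problem for an analysis of all eligible workers; it does not help one restricted to questionnaire participants.

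A reader might infer that the secondary outcomes will be analysed as change from T0. The text says only that a longitudinal multilevel analysis is used, which is compatible with keeping T0 as a response. The role of T0 may properly be settled in the analysis plan.

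**Conclusion.** The concern holds in conditional form. T0 is a post-first-consultation measurement, and the stated rule allows any significant T0 difference to be adjusted for. Following it can remove part of the intervention effect.

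The size cannot be derived from the documents. For the primary outcome it is roughly 5 to 17% of the log HR under assumed shifts of 0.2 to 0.3 SD and covariate hazard ratios of 1.5 to 1.6, and nil at 0.1 SD or below. Attenuation further assumes that the shift is favourable.

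A reader might infer that the effect is certain to be attenuated, or that 16 to 28% of a planned log HR is lost. The documents support neither. They show no T0 shift and plan no hazard ratio, and those percentages leave out the non-collapsibility in Step 3. This is a cheap improvement to the analysis wording, not a flaw in the primary outcome or the sample size.

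**What to change.** - In the time-to-RTW models, replace the significance-triggered rule with a pre-specified set of covariates fixed before the first consultation: age, gender, education, previous-year sick leave, history of mental disorders, contract type and working hours.
- Leave OP diagnosis and T0 expectations out of the main model.
- Describe T0 throughout as measured after the first consultation.
- Report models adjusted for T0 values as a sensitivity analysis, giving possible selection or consent differences after OP allocation as the reason.
- For questionnaire outcomes, report arm differences at T1, T2 and T3, and state that T0-adjusted estimates exclude any effect of the first consultation.

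The cost is analysis wording; no data collection or sample size changes. The downsides are slightly less precision, and that any selection imbalance in the T0 measures is addressed only in the sensitivity analysis.

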#### Primary outcome

The primary outcome is the time to full RTW. For this purpose the number of calendar days between the first day of sickness absence due to CMD and the first day of full RTW is calculated. Working the same hours as prior to the sickness absence in own or equivalent work for at least 4 weeks is considered full RTW. This means that reporting sick within 4 weeks of full RTW is not considered as a new period of sickness absence.

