### Sample size

A power analysis was performed to determine the sample size needed to detect a difference between the control and intervention group with respect to the time workers fully return to their work (primary outcome measure). Proportions of full RTW were adopted from previous studies [7,30]. It was assumed that in the usual care (control) group 55% of the workers would have returned to work after 3 months and 75% after 6 months, whereas in the intervention group these figures would be 75% and 90%, respectively. With a power of 80% at a 0.05 alpha level, assuming an ICC of 0.025 and taking into account a correction factor for the clustered design, it was calculated that 2 × 97 workers would be needed to detect the difference after 3 months and 2 × 110 workers for the difference after 6 months. Allowing for 5% attrition on the sick leave data, a total of 232 workers need to be included.

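### Full returns between the first OP meeting and registry selection are excluded: selection on the primary outcome after randomised care has begun, with direction and size uncertain

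*Protocol article*

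**What the plan says.** All places are in the Protocol article.

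- **Recruitment of participants**, second inclusion criterion, listed as applying to the study: the worker must be "on current sick leave when selected from the registration system of the OHS after the first meeting with the OP".
- **Same section**, in the paragraph on the questionnaire sample: "These workers are selected from the registration system of the OHS after their first consultation with the OP". The lag from consultation to selection is not given.
- **Same section**, first paragraph, on the registry data: "From all eligible workers data on sick leave and RTW will be extracted from the registration system of the OHS anonymously". Eligibility there also requires being on CMD sick leave and having had a first meeting.
- **Study design**: "Data on sick leave and RTW of all invited workers are anonymously extracted from the registration system of the OHS during 1-year follow-up".
- **Intervention/guideline-based care**: under the trained guideline, early involvement means "first assessment and start of counselling about 2 weeks after the worker reported sick".
- **Primary outcome**: the "number of calendar days between the first day of sickness absence due to CMD and the first day of full RTW is calculated". A full return counts once it has lasted at least four weeks.
- **Statistical analysis**: survival analysis allowing for clustering by OP.

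**The concern.** Exposure to randomised care begins at the first OP meeting. The entry condition is tested at a later date and asks whether the worker is still absent, that is, whether the primary event has not yet happened. A worker who goes back fully in between, and stays back, is a success under the allocated care but never enters the comparison. If training works from the first consultation, more such workers are lost from the intervention arm, and the arms compared are differently depleted remainders.

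The exclusion is not needed for the registry outcomes. Return dates are extracted anonymously without contacting the worker. Being absent at selection matters only for inviting people to fill in questionnaires.

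Nor can analysis fully repair it. Left-truncation methods deal with late entry, but they cannot show an effect that acted before entry on workers who were never enrolled.

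**Working it through.** **Inputs.** From Sample size: "in the usual care (control) group 55% of the workers would have returned to work after 3 months and 75% after 6 months"; "in the intervention group these figures would be 75% and 90%, respectively". The lag is assumed to be 1 to 4 weeks.

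**1. The plan's own figure.** The usual two-proportion formula (two-sided 0.05, 80% power) gives 89 per arm at 3 months and 100 at 6 months. The design effect with 232/60 = 3.87 workers per OP is 1 + 2.87 × 0.025 = 1.072, giving 96 and 108 against the stated 97 and 110. Then 220/0.95 = 231.6, rounded up to the stated 232. So these proportions are the plan's working assumptions.

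**2. Share removed.** Constant weekly hazards over 13 weeks: control −ln(0.45)/13 = 0.0614; intervention −ln(0.25)/13 = 0.1066; ratio 1.74. The share returned by lag L is 1 − exp(−hazard × L).

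| Lag | Control | Intervention |
|---|---|---|
| 1 week | 6.0% | 10.1% |
| 2 weeks | 11.6% | 19.2% |
| 4 weeks | 21.8% | 34.7% |

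**3. Effect on the Cox hazard ratio, same entry time in both arms.** Large simulated samples, 52 weeks, clock and lag both starting at the first meeting. Repeat runs agree to within about 0.03.

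| Scenario | All workers | 2-week lag | 4-week lag |
|---|---|---|---|
| Curves through the plan's 3- and 6-month proportions (HR 1.74, then 1.56) | 1.68 | 1.67 | 1.65 |
| Constant HR 1.74 | 1.73 | 1.73 | 1.73 |
| Constant HR 1.74, gamma frailty variance 0.5 | 1.48 | 1.44 | 1.41 |
| Early effect: HR 2.0 for 6 weeks, then 1.3 | 1.57 | 1.49 | 1.40 |
| Same early effect, frailty variance 1 | 1.29 | 1.18 | 1.09 |
| Delayed effect: HR 1 for 3 weeks, then 1.74 | 1.57 | 1.68 | 1.73 |

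Only the first row uses the plan's figures throughout. The early-effect, delayed-effect and frailty inputs are assumptions.

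**4. Fixed-time differences on the plan's curves.** With the first meeting on day 14 and lags of 0, 1, 2 and 4 weeks, the 3-month difference is 0.199, 0.197, 0.192 and 0.176. The 6-month difference is 0.159, 0.163, 0.166 and 0.172. One shrinks and the other grows.

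**5. Different entry times by arm.** The clock runs from the first day of absence, so a worker selected on day 28 could not have had the event on days 1 to 28. If trained OPs see workers sooner and this is ignored:

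| Selection day, intervention / control | True HR 1.73 becomes | True HR 1.00 becomes |
|---|---|---|
| 21 / 28 | 1.87 | 1.07 |
| 21 / 35 | 2.04 | 1.13 |
| 28 / 21 | 1.59 | 0.94 |

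With delayed entry modelled, every case returns to about 1.73 or 1.00.

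**The case against.** A reader might infer that the criterion biases the trial towards no effect. The documents do not support a fixed direction. On the plan's own rates with equal entry times the hazard ratio hardly moves. Marked attenuation needs an effect concentrated in the first weeks, strong heterogeneity between workers, or both, and the plan quantifies neither. The guideline's opening step is orientation and diagnosis, active intervention follows when recovery stalls, and follow-up meetings are three weeks apart. A delayed effect is therefore at least as plausible, and then the estimate rises. Earlier contact by trained OPs also pushes it away from null. This part of the objection stands.

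Second, the first paragraph of Recruitment of participants defines registry eligibility without mentioning selection. Selection from the system is described for the questionnaire sample, and checks such as language and suicidality suit people who are contacted. On that reading the registry set may already retain the early returners. This stands as a possible reading, but it does not settle the matter: that paragraph too requires the worker to be on sick leave after a first meeting, the criteria are headed as applying to the study, and Study design confines registry data to invited workers. No passage clearly keeps those who returned before selection.

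Third, moving the criterion to the first meeting is not enough alone, because the timing of that meeting is something the trained guideline aims to change. This also stands, and the fix below allows for it.

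**Conclusion.** The point holds as a design weakness: entry depends on the primary event not having occurred by a date after randomised counselling began, and two sections disagree on which workers supply the registry data. If training works early, the loss differs by arm (for example 12% against 19% at an assumed 2-week lag).

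The consequence for the estimate is uncertain in sign and size. With equal entry times it is negligible under the plan's own rates (1.68 to 1.65 at 4 weeks). It is towards null with an early effect (1.57 to 1.40) or heterogeneous workers (1.48 to 1.41), and away from null with a delayed effect (1.57 to 1.73). If trained OPs see workers one to two weeks sooner and delayed entry is ignored, a true 1.73 becomes 1.87 to 2.04, and no effect looks like 1.07 to 1.13. All of this rests on the assumed lag; at a week or less the common-entry effect is small. The case for change is that the exclusion serves no purpose for the registry outcomes and is cheap to remove, not that a large bias has been shown.

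**What to change.** 1. Reconcile Study design with Recruitment of participants by stating one registry population.
2. For full RTW, partial RTW and sick-leave days, include every worker of a participating OP who is on CMD sick leave at the first OP meeting, whether or not still absent when the registry is searched. Keep the current-leave condition for the questionnaire sample only.
3. Keep the clock at the first day of absence, but enter each worker into the risk set at the first meeting (left truncation), and report the time from absence to first meeting by arm. The alternative is to anchor the cohort on the first day of registered CMD absence, which the arm cannot affect. As eligibility rests on the OP's diagnosis, that works only if the registry holds a CMD reason for workers who return before any meeting; the article does not say.

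**Cost.** One sentence, one change to the registry query and a delayed-entry term in the survival model. No new data or visits are needed for the first option, since the registry already identifies workers after a first consultation. The small downside is that the registry and questionnaire sets will differ and must be labelled.
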